
### Study design

This intervention study examines the effects of a 12-session healthy lifestyle behavior program (focused on physical activity, nutrition, sleep, and stress management) administered in an individual format as an adjunct to usual care psychotherapy (one healthy lifestyle session per week), compared with a usual care psychotherapy-only control condition. The control group will only attend the outcome assessments and usual care psychotherapy sessions. Therefore, the design relies on a between-groups comparison of the two conditions. Referrals for continued care/therapy beyond the study intervention phase are provided by the study team, and participants assigned to the control group are eligible to complete the health intervention after the conclusion of their participation in the control arm.

### Measures

#### Outcome assessment sessions

Four assessment sessions provide an indication of treatment-related outcomes. These sessions are conducted in person at a University-based laboratory at our study site in Ft. Lauderdale, FL (U.S). The first assessment (baseline) is conducted prior to the first week/study onset in each condition. The second assessment (post-treatment) is conducted at the 3-month time point (after the last healthy lifestyle session in the experimental condition). The third and fourth assessments (follow-up) are conducted at the 6-month and 12-month time points. Each assessment session consists of the same outcome measures: blood pressure, lipids, body mass index (BMI), arterial stiffness, endothelial function, heart rate variability (HRV), physical activity, nutrition, perceived stress, sleep (quantity, efficiency, quality, and restfulness), and psychological measures (PTSD symptoms, depressive symptoms). Results of the lipid measures and blood pressure are reviewed with participants following each assessment, and it is recommended to those with clinically elevated levels that they consult with their primary care physician or other medical provider about such findings.

Due to potential confounding effects on lipids and/or blood pressure, participants are asked to refrain from caffeine and strenuous exercise for 3 h, and smoking for 30 min, prior to assessment sessions. These sessions are scheduled early in the morning (approx. 8:30 a.m.) due to the requirement of fasting for lipid assessment. Non-compliance with restrictions requires rescheduling. After the lipid assessment a standardized snack (granola bar, and water/juice) is provided. A doctoral research assistant (under the direction of the PI) leads each assessment session. The data collection for the assessment sessions lasts approximately 90 min. Assessment of the following variables involving physical measurement is conducted first:

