Stress-related and emotional factors have been identified as an early candidate mechanism for PTSD/CVD relationships, with various responses to acute and chronic stress being implicated in this relationship (Smith et al., 2020a,b). For example, PTSD severity was shown to be related to delayed cardiovascular recovery following a general (not trauma-related) laboratory oral speaking stressor (Kibler, 2018). Delayed cardiovascular recovery in the lab has been associated with greater carotid intima-media thickness, as well as elevated resting blood pressure measured 3 years after lab assessment of recovery (Steptoe et al., 2006; Steptoe and Marmot, 2005). Perceived threat (a pervasive maladaptive cognitive response in PTSD) mediated these physiological disruptions (Kibler, 2018). Research has identified cognitive appraisals, including perceived threat, as key factors to address in PTSD (Iverson et al., 2015). Although the implications of cognitive appraisals for health behaviors in PTSD have not been adequately researched, relationships of appraisals to stress are evident, and Lazarus and colleagues' Cognitive Appraisal Theory (Lazarus and Folkman, 1984) suggests that the types of disrupted cognitions evident in PTSD may interfere with the pursuit of healthy behaviors such as physical activity (Folkman et al., 1986). Interventions to address cognitive appraisals may reduce stress-related CVD risk in PTSD by enhancing the ability to cognitively cope with stressors and engage in healthy behaviors.

The purpose of the present paper is to detail our approach to the study protocol, focusing on the scientific rationale and methodological details. It is hypothesized that the healthy lifestyle intervention will result in greater improvement in vascular function (i.e., endothelial function, arterial stiffness), physical activity, nutrition, sleep, and stress, above and beyond the effects of standard trauma therapy.

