The first module includes psychoeducation on physical activity (health benefits of physical activity and the health risks associated with physical inactivity and overweight) in session 1, as well as implementation of an exercise regimen and discussion of some of the inherent challenges. Participants are encouraged to begin a physical activity regimen that is consistent with recommendations for a healthy lifestyle (aerobic exercise at least 20 min 2–3 times per week). However, interventionists instruct participants to work toward exercise goals that can be incorporated into their lifestyles and maintained. In addition, participants walk for 20 min with the interventionist during intervention sessions 2–5. Session 2 includes discussion of healthy food choices, health risks associated with unhealthy foods, appropriate caloric intake for weight loss (as applicable), reading food labels, fat, vitamin, and sugar content, and setting dietary goals. The interventionist also helps participants distinguish diets from lifestyle changes, emphasize self-monitoring of foods, and helps participants build strategies for nutritional self-control. Nutritional recommendations include a balanced diet, enhancing consumption of fruits and vegetables, and reducing sugars, fat/saturated fat, and caloric intake (as appropriate per participant goals). During sessions 3 and 4, the participant and interventionist work together to analyze current nutritional habits and plan a healthier nutritional plan. Session 3 includes discussion of participant efforts to incorporate physical activity and healthy nutrition into their lifestyle, and the potential for social support to be helpful in behavior change. This session also addresses stress and eating. Interventionists closely monitor the stress coping skills of participants and discuss potential distress associated with giving up previously used unhealthy eating approaches to cope (especially in coping with PTSD symptoms). To address potential desire to be overweight for protection against abuse, alternative methods of achieving a sense of safety are discussed. Session 4 focuses on the skills of shopping for healthy food, planning healthy meals, and reducing behavioral cues/triggers for binge eating and unhealthy eating (e.g., storing foods out of sight, strategies for parties, special events and restaurants, managing emotions). Sessions 5 and 6 will include further discussion of progress and challenges with the physical activity and nutrition regimens.

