## Discussion

The presently described project examines the potential positive health effects of a relatively short-term healthy lifestyle intervention for adults with PTSD and CVD risk. In a pilot study, our health behavior intervention program had the greatest impact on sleep and physical activity (Kibler et al., 2023). Given the prior data on sleep disruption and lower physical activity in PTSD (Harte et al., 2015; Lamarche and De Koninck, 2007), such outcomes in the present study would be considered major changes that would likely enhance health and quality of life if changes are maintained for individuals with PTSD.

There is preliminary evidence that simultaneous physical activity and nutritional intervention may be more effective for impacting eating habits than focusing on the respective behaviors sequentially (Johnson et al., 2014; Vandelanotte et al., 2005). Overlapping modules in the proposed program will encourage building skills for a healthier lifestyle early in the intervention. In addition, focusing on multiple health behaviors at once may permit participants' detection of interacting variables (e.g., a participant does not sleep well on days that they do not exercise) (Johnson et al., 2014; Prochaska et al., 2008). Physical activity and nutrition are emphasized in sessions 1–5; participants are instructed to continue implementing their physical activity and nutritional plans throughout the intervention, and to continue these regimens beyond completion of the program. Our efforts to address sleep in conjunction with other health behaviors may also confer a synergistic effect that is greater than the impact of each component alone (Nagaya et al., 2007; Prochaska et al., 2008). One study showed a positive association between exercise intervention and improved sleep for individuals with PTSD (Björkman and Ekblom, 2021).

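### The pre-visit rule bars only strenuous exercise for 3 h, so the moderate exercise coached in one arm may precede later visits and be mixed with sustained change

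*Protocol article*

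**What the plan says.** In the protocol article, under Outcome assessment sessions, the rule is that "participants are asked to refrain from caffeine and strenuous exercise for 3 h, and smoking for 30 min, prior to assessment sessions". The reason given is "Due to potential confounding effects on lipids and/or blood pressure". The same visit also measures endothelial function, peripheral augmentation index (PAIx) and heart rate variability (HRV), which that reason does not mention. On timing: "These sessions are scheduled early in the morning (approx. 8:30 a.m.) due to the requirement of fasting for lipid assessment". On enforcement: "Non-compliance with restrictions requires rescheduling". All four assessments use the same outcome measures.

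Under Health behavior/lifestyle intervention, the experimental arm is encouraged to take up "aerobic exercise at least 20 min 2–3 times per week", and "participants walk for 20 min with the interventionist during intervention sessions 2–5". The Discussion adds that participants are told "to continue these regimens beyond completion of the program". Under Study design, controls attend only the assessments and their psychotherapy.

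The Introduction places endothelial function and arterial stiffness first among the hypothesised improvements.

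**The concern.** The rule is narrow in intensity (strenuous only) and in time (3 h). The exercise that the trial promotes is largely of another kind: 20-minute walks, and aerobic bouts that participants build up to at their own pace. Most of it falls outside the rule, so the rescheduling provision does not reach it either.

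Because one arm is coached and the other is not, recent exercise can become more common in the experimental arm once the program has begun. At baseline no coaching has taken place, so no such difference is expected. An imbalance that appears only after baseline stays in the change score. The Data analysis plan adjusts for variables on which the groups differ at baseline, and this would not be one of them.

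At stake is what an arm difference means. The trial asks about cardiovascular risk reduction, and the Discussion stresses longer-term change. If some of the difference is the after-effect of a bout that morning or the day before, the result answers a mixed question.

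**Working it through.** **1. What the rule permits.** Visit at about 8:30 a.m. minus 3 h gives about 5:30 a.m.

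| Exercise before the visit | Allowed as worded? |
|---|---|
| Strenuous, after about 5:30 a.m. that day | No |
| Strenuous, the previous day or evening | Yes |
| Walking or moderate, the previous day | Yes |
| Walking or moderate, that morning up to the visit | Yes |

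**2. Whether the article shows a way to detect or correct it.** The accelerometer (Accelerometry section) is worn for the week after each visit, not before it. The activity questionnaire (Physical activity section) is described as covering the past week, not time since the last bout. The Data analysis plan handles baseline differences only. A visit form in the full protocol may record recent exercise. Its absence from the article is not held against the plan, and the point rests on the rule as stated.

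**3. An illustration of size.** The plan gives no figure on this point to reproduce. The formula is:

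shift (SD) = (p_E − p_C) × a

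Here p_E and p_C are the shares of visits with exercise in the prior 24 h in the experimental and control arms, and a is the acute effect still present.

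Inputs:
- From the article: 2–3 bouts per week in the experimental arm.
- Assumed: full adherence; bouts on separate days placed at random; 0–1 bout per week in controls; a = 0.2–0.5 SD, undiminished across the 24 h.

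Exposure:
- p_E = 2/7 to 3/7 = 0.286 to 0.429.
- p_C = 0 to 1/7 = 0 to 0.143.
- Smallest gap: 0.286 − 0.143 = 0.143. Largest gap: 0.429 − 0 = 0.429.

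Shift:
- Low: 0.143 × 0.2 = 0.03 SD.
- High: 0.429 × 0.5 = 0.21 SD.
- If the effect instead fell linearly to zero over 24 h, its average would be half of a, and the range would be about 0.01–0.11 SD.

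**4. Set against the planned effects.**
- Lipids, d = 0.50: 0.029/0.50 = 6% to 0.214/0.50 = 43%.
- Endothelial function, d = 0.55: 0.029/0.55 = 5% to 0.214/0.55 = 39%. Arterial stiffness, at d = 0.56, is nearly the same.

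These are ratios of magnitude. They do not say which way the shift goes.

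**5. Effect on a nominal two-sided 5% test with no lasting effect.** With the planned 81 completers per arm, SE = √(2/81) = 0.157 SD.
- Shift 0.029: 0.029/0.157 = 0.18, and rejection is 5.4%.
- Shift 0.214: 0.214/0.157 = 1.36, and rejection is about 28%.

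The upper figure needs full adherence, no control exercise and no decay, all at once.

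**The case against.** The strongest objection is that the documents nowhere say how large or how long-lived an acute exercise effect is. The article concedes only that strenuous exercise may confound lipids or blood pressure, and sets 3 h. Extending that to moderate exercise, to a longer window and to the vascular measures is inference. This stands: the size is an assumption, and for the vascular measures so is the direction.

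The exposure gap may also be small. Participants are encouraged, not required, to exercise, and they set goals that they can maintain. Low physical activity is only one of several qualifying health risks, so some controls may already exercise. This stands too, and it pulls towards the low end of the range.

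A third objection is that recent exercise is part of how a regularly active person lives, so its effect may belong to the treatment effect. That is arguable. But the article itself treats recent exercise as a confounder to be controlled at the visit, and its stated interest is longer-term change. A rule built on that logic should cover the exercise that the trial promotes.

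A reader might infer that coached participants will be measured within hours of a workout, or that acute effects could account for the planned benefit. The documents support neither. Strenuous exercise is barred from about 5:30 a.m., and a hard session before then is unlikely. The realistic gaps are moderate exercise that morning and any exercise the day before. Even the top of the range shown is less than half of the planned vascular and lipid effects.

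**Conclusion.** The point holds as a gap in how the visits are standardised. The pre-visit rule does not cover most of the exercise coached in one arm, its stated reason leaves out the lead vascular outcomes and HRV, and any resulting imbalance would arise after baseline, where neither change scores nor the planned adjustment would remove it. Part of an arm difference could therefore reflect the last bout.

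On the stated assumptions the shift is about 0.03–0.21 SD, and smaller if the effect fades within 24 h. No size, duration or vascular direction can be taken from the documents, so the finding is a risk of bias that is cheap to reduce. It is not a demonstrated bias. It merits a change but does not undermine the design.

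**What to change.** Under Outcome assessment sessions, from a dated amendment and for both arms:

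- Extend the exercise instruction to any planned moderate or vigorous exercise over a longer window before each assessment, for example 24 h.
- State that the restriction also protects the EndoPAT measures (endothelial function and PAIx) and HRV, not only lipids and blood pressure.
- Keep the existing rescheduling rule for breaches. The caffeine and smoking terms need no change on this account.
- Record time since last exercise at every visit, and report it by arm and visit.

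Time since last exercise is a post-randomisation variable that the intervention itself may alter. Any analysis that uses it should be labelled descriptive sensitivity work. Excluding visits because of recent exercise should not be the main safeguard, since that can introduce selection between arms.

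The cost is new reminder wording, one or two lines on the visit checklist, and some extra rescheduling, which would fall mainly on the experimental arm. The trial is ongoing, so earlier visits will have been made under the old rule. The amendment date should be kept in the data so that visits under each rule can be told apart.

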#### Fasting lipid profile

The Cholestech LDX System is utilized to assess lipids. The Cholestech is designed for point of service lipid analysis using finger stick capillary whole blood. It uses reflectance photometry to obtain lipid results that are available within 4 min. Lipid values derived from the Cholestech are highly correlated with serum-derived reference values (*r* values 0.96–0.98) (Cobbaert et al., 1993; Polito et al., 2000). Triglycerides, total cholesterol, high-density lipoprotein (HDL), and low-density lipoprotein (LDL) will be measured. Team members who conduct this procedure receive extensive training and practice, including training in precautions with biohazardous wastes. Blood glucose will be considered as an additional variable of interest in secondary analyses.

#### Blood pressure

The participant sits quietly for 5 min, after which three seated, automated systolic blood pressure (SBP) and diastolic blood pressure (DBP) readings (IntelliSense model 5243175; Omron Healthcare Inc.) are taken at 2-min intervals from the left arm to minimize confound with the EndoPat (referenced below for endothelial function and arterial stiffness), for which the right arm is utilized for the test.

#### Body mass

Body weight is measured in pounds with a digital physicians' scale, which permits valid measurement to the nearest tenth of a pound. Height is measured, and the participant's weight is contrasted with height-based norms for the purposes of determining BMI and overweight/obesity status. Measures of waist-to-hip ratio are examined, along with body weight alone, in evaluating body mass/high weight in secondary analyses.

#### Endothelial function

Peripheral arterial tonometry (PAT) signals are obtained using the EndoPAT device (Itamar Medical Inc., Caesarea, Israel), which has been validated and used previously to assess peripheral arterial tone (Halligan et al., 2004; Lavie et al., 2000). EndoPat -derived endothelial function has demonstrated convergent validity with flow-mediated dilation indexed by brachial artery ultrasound scanning (Kuvin et al., 2003) and independent prediction of adverse cardiac events (over 7 years), established endothelial dysfunction, and actual cardiac disease (Bonetti et al., 2004; Rubinshtein et al., 2010). Specially designed finger probes comprise a system of inflatable latex air cuffs connected by pneumatic tubes to an inflating device controlled through a computer algorithm. A constant counter pressure (pre-determined by baseline DBP) is applied through the air cushions. This prevents venous pooling, avoids venoarteriolar reflex vasoconstriction, and there is no arterial blood flow occlusion. Pulsatile volume changes of the distal digit induce pressure alterations in the finger cuff, which are sensed by pressure transducers and transmitted to and recorded by the EndoPAT device. Blood pressure and heart rate are measured using an automated blood pressure monitor (IntelliSense model 5243175; Omron Healthcare Inc.). Endothelial function is measured via an RH–PAT index (Hamburg et al., 2008; Rubinshtein et al., 2010). An RH protocol consists of a 7-min baseline measurement, after which a blood pressure cuff on the right arm is inflated to 60 mmHg above baseline SBP or at least 200 mmHg for 5 min. Occlusion of pulsatile arterial flow is confirmed by the reduction of the PAT tracing to zero. After 5 min, the cuff is deflated, and the PAT tracing is recorded for another 5 min. The ratio of the PAT signal after cuff release compared with baseline is calculated through a computer algorithm, automatically normalizing for baseline signal, and indexed to the contralateral arm. The calculated ratio reflects the RH index.

#### Arterial stiffness

The EndoPat device is also used to assess arterial stiffness. The system calculates peripheral augmentation index (PAIx) from the radial pulsewave analysis (Meeme et al., 2017). PAIx is automatically calculated as the ratio of the difference between the waveform's early and late systolic peaks relative to the early peak (P2–P1/P1), expressed as a percentage. EndoPat arterial stiffness measures have convergent validity with the SphygmoCor device (Ring et al., 2014; Segers et al., 2020), the gold standard for non-invasive central blood pressure and arterial stiffness assessment, and other non-invasive methods (Haller et al., 2007; Perrault et al., 2019). Predictive validity of cardiovascular risk (Framingham), pre-eclampsia, and kidney dysfunction has also been documented for EndoPat arterial stiffness measures (Li et al., 2023; Meeme et al., 2017).

#### Heart rate variability (HRV)

The HRV assessment is also conducted using the EndoPat device via pulsatile volume changes based on the plethysmography waveforms. The frequency domain considers two spectral components and physiological origins: low-frequency (LF; 0.04 to 0.15 Hz; sympathetic modulation) and high-frequency (HF; 0.15 to 0.40 Hz; parasympathetic modulation). The LF/HF ratio reflects the sympathetic balance. The time domain considers the mean of normal sinus rhythm pulse-intervals (MeanNN), the standard deviation of NN-intervals (SDNN), the percentage of successive NN-intervals above 50 ms (PNN50), root-mean-square of successive differences (RMSSD) of NN-intervals, and triangular index (Shaffer and Ginsberg, 2017). SDNN provides an index of total variability, as a function of both parasympathetic and sympathetic influences; RMSSD represents the predominant parasympathetic modulation in cardiac function (Allen et al., 2007). EndoPat HRV measures have been shown to be reliable and to have convergent validity with other non-invasive methods (Linder et al., 2014).

An online computer assessment is utilized for the following self-report measures:

#### Physical activity

The International Physical Activity Questionnaire (7-day long form) is a 27-item measure, developed through international collaboration to be a standard for physical activity assessment. It evaluates time spent in moderate and vigorous activity, walking, and sedentary behaviors over the past week, aligning with current activity guidelines (e.g., 134–135). The IPAQ demonstrates strong test-retest reliability (ICC = 0.66–0.88; Craig et al., 2003) and moderate validity, with correlations of *r* = 0.30–0.50 compared to accelerometer data (Hagströmer et al., 2006). The IPAQ's standardized format ensures consistent and valid assessment of physical activity patterns across diverse populations.

